#### Primary Outcome Measures

The primary objective of this pilot study is to determine feasibility of a full-scale RCT. Specific outcomes include (1) recruitment rate, calculated as the percentage of eligible participants among those approached to determine if current eligibility criteria are too open or restrictive; (2) intervention completion rate, calculated as the percentage of recruited participants who complete the 8-week treatment (i.e., take ≥80% of the medicine); and (3) data completion rate, calculated as the percentage of recruited participants who complete the 8-week and 4-week follow-up assessments. The trial may be feasible if the recruitment rate ≥30%, intervention completion rate ≥80%, and data completion rate ≥80%, and not feasible if the recruitment rate <15%, intervention completion rate <70%, and data completion rate <70%. When the parameters fall between the two, it might be feasible if appropriate changes are made (Eldridge et al., 2016).

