#### Statistical Analysis

The primary feasibility outcomes will be reported descriptively with percentage, mean or median, standard deviation, or 95% confidence interval. As a pilot, the study is not powered to detect a statistically significant difference between groups. The treatment effect will be assessed with mean difference between two groups and confidence intervals of 75%, 85%, and 95%. A figure showing these CIs, minimum important difference, and the null value will help assess both statistical significance and the potential for clinical significance (Bell et al., 2018). All analyses will be conducted according to the intention-to-treat principle. Last observation carried forward will be used for imputing missing data because tinnitus is a chronic and constant symptom. Descriptive statistics will be computed for each of the analyzed variables. Exploratory inferential analysis will be performed using repeated-measures ANCOVA. Mean differences from baseline to end of treatment in each group will be examined by paired *t*-test or Wilcoxon signed rank test. Subgroup analysis on those with or without hearing loss, and those with unilateral or bilateral tinnitus will be made. All statistical tests will be two-sided, and *p* < 0.05 is considered statistically significant. The statistical software of SPSS 23.0 will be used for analysis.

Adverse events will be categorized and percentage of those experiencing some adverse events and serious adverse events will be documented. Chi-square tests will be performed to examine differences in the proportion of total and categories of adverse events within each group.

It is anticipated to find some preliminary evidence about the clinical effectiveness of BHT on chronic tinnitus, to identify if it is feasible to conduct a full-scale RCT of BHT and necessary changes to the protocol if possible. Statistical comparisons between groups may be misleading due to the many potential problems arising from small samples and low power. The results from statistical comparisons will be treated with great caution, and reported only with explicit reference to statistical power.

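### The pilot's *not feasible* rule joins all three lower limits with 'and' and does not expressly say what follows when one rate fails and the others do not

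*Protocol article*

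**What the plan says.** All of the rule stands in the Protocol article, Primary Outcome Measures. The section opens with the aim: "The primary objective of this pilot study is to determine feasibility of a full-scale RCT". It then defines three rates:

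- Recruitment: "calculated as the percentage of eligible participants among those approached".
- Intervention completion: "calculated as the percentage of recruited participants who complete the 8-week treatment (i.e., take ≥80% of the medicine").
- Data completion: "calculated as the percentage of recruited participants who complete the 8-week and 4-week follow-up assessments".

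Three statements turn these rates into a verdict:

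- Upper: "The trial may be feasible if the recruitment rate ≥30%, intervention completion rate ≥80%, and data completion rate ≥80" per cent.
- Lower: "not feasible if the recruitment rate <15%, intervention completion rate <70%, and data completion rate <70" per cent.
- Middle: "When the parameters fall between the two, it might be feasible if appropriate changes are made".

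Statistical Analysis adds reporting but no decision rule: "The primary feasibility outcomes will be reported descriptively with percentage, mean or median, standard deviation, or 95% confidence interval".

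**The concern.** The upper and lower statements have the same form: three limits joined by 'and'. For a decision to go ahead, requiring all three is sensible. For a decision to stop, the same form means that one rate can fail badly without producing the *not feasible* verdict, provided another rate stays above its lower limit.

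The Introduction lists recruitment, acceptability and adherence as separate feasibility questions, and a serious failure on any of them could make the full-scale trial unworkable as designed. If the text does not settle how a failed rate combines with adequate ones, that verdict is left to judgement after the data are known, on the question that is the pilot's primary objective.

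**Working it through.** **Inputs.** The limits come from Primary Outcome Measures: recruitment 15% and 30%, both completion rates 70% and 80%. The planned total of 24 comes from Sample Size Estimation. The number of patients approached is not stated, so 80, 120 and 160 are assumed. The true rates below are also assumed.

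**Step 1: count the combinations (text only).** Call each rate U (at or above its upper limit), M (middle) or L (below its lower limit).

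- All combinations: 3 × 3 × 3 = 27.
- No rate in L: 2 × 2 × 2 = 8.
- At least one rate in L: 27 − 8 = 19, made up of 12 with one L, 6 with two and 1 with three.

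**Step 2: apply the three statements.** UUU is feasible and LLL is not feasible. The rest depends on the middle statement.

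| Reading of the middle statement | Results it covers | Results with no express verdict | Results with at least one L not called *not feasible* |
|---|---|---|---|
| Strict: every rate is in its own middle band | MMM only (1) | 27 − 3 = 24 | 18 of 19 |
| Broad: everything that is neither UUU nor LLL | 27 − 2 = 25 | 0 | 18 of 19 |

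The readings differ on what a mixed result is called, but agree that 18 of the 19 combinations with a failed rate are not called *not feasible*. Of the 24 without an express verdict on the strict reading, 24 − 18 = 6 mix only U and M. Feasible with changes is the natural meaning for those 6, so only the 18 are in real dispute.

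**Step 3: an example.** Intervention completion 50% (12 of 24, or 6 of 12 if only the BHT arm counts), recruitment 40%, data completion 90%. The pattern is U, L, U. On the strict reading it has no express verdict. On the broad reading it might be feasible with changes.

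**Step 4: how often the two stop rules would fire.** With n = 24, a rate below 70% means at most 16 (16/24 = 66.7%, 17/24 = 70.8%). With n = 12 it means at most 8 (8/12 = 66.7%, 9/12 = 75%). Exact binomial probabilities, treating the three rates as independent:

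P(any L) = 1 − (1 − p_rec)(1 − p_int)(1 − p_data); P(all L) = p_rec × p_int × p_data

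- *True rates 40%, 50%, 90%.* p_int = P(Bin(24, 0.5) ≤ 16) = 0.968, p_data = P(Bin(24, 0.9) ≤ 16) = 0.0017, p_rec ≈ 0. P(any L) = 96.8%; P(all L) ≈ 0.
- *True rates 40%, 90%, 90%.* P(any L) = 1 − (1 − 0.0017)² = 0.3%.
- *True rates exactly 30%, 80%, 80%.* p_int = p_data = P(Bin(24, 0.8) ≤ 16) = 0.0892; p_rec is at most 0.0006 (80 approached). P(any L) ≈ 1 − 0.911² = 17%.
- *The same, with intervention completion judged on 12 BHT patients.* p_int = P(Bin(12, 0.8) ≤ 8) = 0.205. P(any L) ≈ 1 − 0.795 × 0.911 = 28%.

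The two completion rates are unlikely to be independent, since a patient who leaves early tends to fail both. Positive dependence lowers the last two figures. They cannot fall below the larger single probability: 8.9% with 24 patients, 20.5% with 12.

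**The case against.** A reader might infer that one failed rate can never stop the full-scale trial. The text does not support that. It says 'if', not 'only if', and uses 'may' and 'might', so nothing binds the investigators to proceed. A reader might also infer that mixed results have no verdict at all. That is true only on the strict reading; on the broad one they all fall under the middle statement, which is itself conditional on changes. The limits may even have been meant rate by rate, so that 50% intervention completion does fail its own limit. These points stand, and they narrow the claim. They do not remove it: on the rate-by-rate reading the text still does not say how one failed rate combines with two adequate ones.

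Nor do the documents show that mixed results are the likeliest outcome. The 27 cells are neither equally likely nor independent, so the count is not a probability.

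The any-one-fails rule is partly a matter of preference. The recruitment rate is meant to show whether the eligibility criteria are too wide or too narrow, and the Discussion expects the results to inform those criteria and reduce withdrawal. A low rate may therefore be repairable. That stands, and is why the proposed verdict is limited to the trial *as designed*.

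Finally, the wording biases no estimate, all three rates will be reported anyway, and a 95% confidence interval is already among the listed summaries. That lowers the severity. The article's being a condensed account does not answer the point, because the article states the rule and its limits in full.

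**Conclusion.** The concern holds in a limited form. As written, the *not feasible* condition is a conjunction of three failures, and the consequence of a single failure is not expressly stated. Under both the strict and the broad reading of the middle statement, 18 of the 19 band combinations with at least one failed rate are not called *not feasible*. That count rests on the text alone. The probabilities rest on assumed true rates, an assumed number approached and independence; they show what the choice of rule does and do not forecast this trial.

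It is a flaw in the stated decision rule for the primary objective, but it does not bar the investigators from stopping and leaves the reported rates untouched. It should be fixed; it is not a fatal defect.

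**What to change.** Keep the thresholds and replace the rule, before the data are seen, with wording to this effect:

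- The limits apply to each rate separately.
- Feasible: all three rates reach their upper limits.
- Not feasible as designed: any one rate is below its lower limit.
- Every other result: feasible only with changes to the criteria that missed.

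State in the same place whether intervention completion is judged on all 24 recruited patients or on the BHT arm, since only that arm takes the medicine and the choice alters how often the rule fires.

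The drafting cost is a sentence or two. The real cost is that a *not feasible as designed* verdict becomes more likely: from practically nil to about 17% when true rates sit exactly at the upper limits, or about 28% with the 12-patient denominator, both under independence. For a trial with true rates of 40%, 90% and 90% the cost is negligible, at 0.3% with 24 recruited.

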#### Secondary Outcome Measures

A comprehensive set of outcome measures is employed to assess mainly the following six domains: tinnitus percept, impact of tinnitus, co-occurring complaints, quality of life, and treatment-related outcomes (Hall et al., 2016).1) Tinnitus Handicap Inventory in Chinese (Cantonese) version (THI-CH)

THI-CH is a 25-item self-administered questionnaire to quantify the impact of tinnitus on daily life. It has been demonstrated to be a reliable and valid measure of self-perceived tinnitus-related distress (Kam et al., 2009).2) Tinnitus functional index in Chinese (Cantonese) version (TFI-CH)

TFI-CH is a 25-item self-administered questionnaire that assesses eight domains of tinnitus impact: intrusiveness, sense of control, cognition, sleep, auditory, relaxation, quality of life, and emotion. It has been demonstrated to be a reliable and valid measure for intake assessment and treatment-related changes (Kam et al., 2018).3) Tinnitus sensation level

The tinnitus pitch and loudness matching will be measured according to Vernon and Meikle’s procedure (Vernon and Meikle, 2003).4) Self-rated visual analogue scale (VAS) on tinnitus loudness and annoyance (McCormack et al., 1988)

VAS is a validated and reliable tool for measuring subjective experience in tinnitus loudness and annoyance (Vernon and Meikle, 2003). It will be measured per ear. If a subject has bilateral tinnitus, the VAS will be measured differently for each side.5) Chinese (Cantonese) version of the Pittsburgh Sleep Quality Index (CPSQI)

The CPSQI is a self-rating questionnaire used to measure the quality and patterns of sleep in adults (Tsai et al., 2005).6) Chinese (Cantonese) version of Hospital Anxiety and Depression Scale (HADS)

The Chinese HADS is a 14-item questionnaire designed to assess the severity of mild, even sub-syndromal degrees of anxiety and depression (Leung et al., 1999).7) Adverse events

Adverse events will be recorded and coded to preferred terms as defined by the Medical Dictionary for Regulatory Activities (MedDRA), version 22.0.

All measurements will be taken at baseline, end of treatment (8 weeks after the first day of treatment), and after the 4-week follow-up. Kidney function will be examined before and after the treatment on those receiving BHT.

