The study objectives are to determine the feasibility of performing a full-scale RCT for evaluating the effectiveness and safety of BHT for patients with chronic subjective tinnitus; to explore whether a TCM formula (BHT) has an additional effect on improving the impact of tinnitus in daily life and psychological function and also the perception of tinnitus after 8-week treatment and 4-week follow-up when compared to informative counseling alone; and to assess the safety of a TCM formula (BHT) in the patient population over the study duration of 12 weeks.

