## Methods

### Design Overview

This pilot study is a randomized, assessor blind, two-arm, parallel superior trial. The trial design was developed conforming to Standard Protocol Items: Recommendations for Interventional Trials (SPIRIT) Guidelines (Chan et al., 2013). The study will be conducted in the Integrative Medical Centre (IMC), CUHK, and the Chinese Medicine Specialty Clinic cum Clinical Teaching and Research Centre at School of Chinese Medicine, CUHK. A total of 24 patients will be recruited and allocated randomly to receive a TCM formula (BHT) and informative counseling or informative counseling alone. The oral BHT herbal granules will be taken twice per day continuously for 8 weeks. The measures of feasibility and potential clinical effectiveness will be collected at baseline, end of the treatment (week 8), and after the follow-up (week 12). This trial will be conducted in accordance with the Declaration of Helsinki and ICH Good Clinical Practice.

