### Randomization and Blinding

A computer-generated random allocation sequence through the block randomization method will be used. A research staff, with no clinical involvement in the trial, will be responsible for keeping the random allocation list and preparing sealed, opaque sequentially numbered envelopes, each containing a random number denoting the allocated treatment. After obtaining written informed consent, another research staff will open the envelopes serially, and refer the eligible patient to receive TCM formula (BHT) and informative counseling or informative counseling alone.

The outcome assessor will be kept blind at the intervention assignment during the whole study period. It is not feasible to blind doctors and patients in this study.

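### Kidney function is tested only in the BHT arm, so the adverse-event comparison can be biased against BHT if abnormal results are counted as adverse events

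*Protocol article*

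**What the plan says.** All places are in the protocol article.

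- **Design Overview:** patients are "allocated randomly to receive a TCM formula (BHT) and informative counseling or informative counseling alone".
- **Secondary Outcome Measures:** adverse events are the seventh secondary outcome: "Adverse events will be recorded and coded to preferred terms as defined by the Medical Dictionary for Regulatory Activities (MedDRA), version 22.0". The general schedule names no arm: "All measurements will be taken at baseline, end of treatment (8 weeks after the first day of treatment), and after the 4-week follow-up". The next sentence does: "Kidney function will be examined before and after the treatment on those receiving BHT". No kidney test or other laboratory safety test is given for the counseling-alone arm.
- **Statistical Analysis:** "Chi-square tests will be performed to examine differences in the proportion of total and categories of adverse events within each group". The section also plans to report the percentage of patients with adverse events and serious adverse events. Tests are two-sided with a 0.05 threshold. Kidney results are not mentioned.
- **Introduction (study objectives):** one objective is "to assess the safety of a TCM formula (BHT) in the patient population over the study duration of 12 weeks".
- **Randomization and Blinding:** the outcome assessor is blind, but "It is not feasible to blind doctors and patients in this study".

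**The concern.** Adverse-event proportions can be compared fairly only if both arms are searched for events in the same way. Here a silent kidney abnormality can come to light in a BHT patient but not in a control, whatever the true risks are. Randomization and a blinded assessor do not correct this, because the difference lies in what is looked for.

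Two things are at stake. First, if abnormal results enter the adverse-event counts, the total is tilted against BHT, and a renal or laboratory category has no test-detected events among controls by design. Second, a change from before to after treatment in the BHT arm has nothing concurrent to be read against. The Introduction itself prefers a controlled pilot because participants can change without any intervention.

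The description of the test adds to the difficulty. It places the comparison within each group, whereas a difference in adverse-event proportions makes sense here only between groups.

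**Working it through.** **Inputs from the protocol article**
- Sample Size Estimation: 10 per arm, 20% dropout, 24 in total. Reproduced: 10 × 1.20 = 12 per arm, and 2 × 12 = 24. Equal arms of 12 are inferred from this.
- Kidney tests in the BHT arm only; chi-square test, two-sided 0.05.

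**Inputs that are assumptions, because the article gives no figure**
- Base risk b: the chance, equal in both arms, that a patient has an adverse event found by ordinary means. Values 10%, 25%, 40%.
- Rate q: the chance of a new abnormality after baseline that only the test reveals and that is recorded as an adverse event, independent of other events. Values 2%, 5%, 10%.

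**Step 1. Spurious excess.** The control proportion is b. The BHT proportion is b + (1 − b)q, since a test finding adds to the total only in a patient with no other event. The expected excess is therefore (1 − b)q, in percentage points:

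| b | q = 2% | q = 5% | q = 10% |
|---|---|---|---|
| 10% | 1.8 | 4.5 | 9.0 |
| 25% | 1.5 | 3.75 | 7.5 |
| 40% | 1.2 | 3.0 | 6.0 |

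The range is 0.60 × 2% = 1.2 to 0.90 × 10% = 9.0 points.

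**Step 2. One finding.** A single finding in a patient with no other event moves the BHT proportion by 1/12 = 8.3 points. In a patient who already has an event it moves the total by zero.

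**Step 3. Chance of at least one finding among 12.** 1 − (1 − q)^12 gives 22%, 46% and 72% for q = 2%, 5% and 10%. In controls it is zero by design. These figures show how readily the question would arise; they are not the size of the bias.

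**Step 4. Effect on the test.** Exact enumeration of the uncorrected Pearson chi-square, 12 against 12, with equal true risk, gives these rejection rates:

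| b | equal testing | q = 2% | q = 5% | q = 10% |
|---|---|---|---|---|
| 10% | 1.5% | 1.9% | 2.9% | 5.9% |
| 25% | 4.4% | 4.6% | 5.1% | 6.6% |
| 40% | 5.9% | 6.0% | 6.3% | 7.3% |

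For q of 2% to 5% the rise is at most 1.4 points (2.9% against 1.5%). At q = 10% it is 1.4 to 4.4 points.

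**Step 5. A renal category.** Test-detected events in controls are fixed at 0. A split of 4/12 against 0/12 already gives chi-square p = 0.029 (Fisher exact p = 0.093), although four findings would be unusual at the rates assumed here.

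**Step 6. After the fix.** With test-detected findings left out of the comparison, the expected spurious excess is 0 and the rejection rates return to the equal-testing column.

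**The case against.** The strongest objection is that the article never says kidney results feed the adverse-event counts. Adverse events are a numbered outcome; the kidney test is a separate sentence after the schedule. Whether a laboratory abnormality counts as an adverse event is often settled in the full protocol or analysis plan, which are not shown. This stands in part. A reader might infer that the comparison is biased as planned; the text does not support that, and only a conditional statement is justified. What does not depend on missing detail is the stated restriction of the test to one arm, next to a stated test on all adverse events.

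It is also fair to say that the between-arm reading of the chi-square test is an inference from wording that points elsewhere. That is so, and the wording itself needs correcting.

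A reader might further infer that every kidney finding shifts the BHT proportion by 8.3 points. That fails for a patient who already has an event. Nor is every abnormal value relevant: the baseline test identifies pre-existing abnormality, and uncontrolled renal disease is an exclusion criterion, so q must be the rate of new abnormality.

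Testing only the patients who take the herbal formula is ordinary monitoring and is not disputed. No sentence of the article plans a conclusion about safety or harm from the kidney change alone, so misreading of it is a risk and not a stated plan.

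Finally, this is a pilot with feasibility as its primary outcome, and the Statistical Analysis section promises great caution with comparisons. That limits the consequence. But the caution given there concerns small samples and low power; unequal ascertainment is systematic and is a different problem.

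**Conclusion.** The point holds in conditional form and is minor. Ascertainment of kidney abnormalities is unequal by design. If such abnormalities are recorded as adverse events, the comparison can be biased against BHT by an expected 1 to 9 percentage points, with only a modest rise in false-positive findings. These sizes rest on assumed rates (new abnormality 2% to 10%, base risk 10% to 40%), equal arms of 12 and equal true risk. Symptomatic events are not affected. Whether or not kidney results are counted, the change under BHT cannot be compared with change under counseling alone.

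**What to change.** Change the analysis wording in three places:

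1. Describe the chi-square tests as comparing adverse-event proportions between the two groups.
2. State that this comparison, overall and by category, counts only events found by methods used equally in both arms, such as spontaneous report and the same questioning at the same visits.
3. List kidney results separately, as individual before and after values for BHT patients, outside the compared tables and with no claim about the difference from control.

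This needs no extra procedure and no change in patient care. The small cost is that the compared adverse-event total omits kidney-test findings, which are shown beside it so that no safety information is lost.
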